### Data collection & statistical analyses

To measure mean percent weight change, we will use EHR weights, which are collected similarly across UC health center visits, and DPP session weights for UC beneficiaries who enroll in DPP. Baseline covariate differences between those with and without attrition will be examined and we will then adjust for any covariates found to be significantly different (*p* < 0.05) between attrition groups in order to satisfy the Missing at Random assumptions of the mixed effects models. Because attrition could be a consequence of our primary outcome (i.e. weight) our missing data may be Missing Not at Random. In this instance we will utilize pattern mixture modeling to impute missing valuies. We will conduct within-subject analysis estimates of UC DPP Initiative effectiveness among those who received a “full intervention dose” (i.e., Group 1 prediabetes awareness letters and enrolled in DPP). For this primary analysis, we will use a mixed effects linear regression model to compare percent weight change within Group 1 subjects 12 and 24 months before DPP enrollment (pre period) and 12 and 24 months after enrollment (post period). Models for the trajectory of percent weight change will be specified with a random intercept for person with nested random slope for time from enrollment measured on a continuum. Average within-person between time-period (post vs. pre-enrollment) differences in the trajectory for % weight change will be modeled using a fixed effect interaction term of time-by-time-period to test for between time-period differences in the rate of % weight change. These models will be fit using a random intercept for person and random slope for time-period (post vs pre). A fixed effect of time-period will be used to estimate the average between time-period difference in % weight change adjusting for the corresponding length of time over which the change was observed. For both models, exploratory post-hoc analyses will also consider additional subject level covariates (age, gender, race, ethnicity, number of co-morbidities, number of DPP sessions attended, education level and years employed at the institution), as well as DPP site. Interactions of the difference over time (rates or mean levels) by these subject characteristics or site will also be explored to evaluate whether there is a differential benefit of the program for certain groups of beneficiaries (i.e., heterogeneity in treatment effect) and across sites. In the presence of statistically significant (*p* < 0.05) interactions, the models will be stratified so as to allow for potential heterogeneity in the covariates as well.

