### Aim 2: reach of UC DPP

To assess reach, we will report the proportion of eligible UC beneficiaries who engage in DPP (attend > 9 and > 16 sessions) and their representativeness of UC beneficiaries overall. Using DPP enrollment and participation data from each campus, we will assess the proportion of eligible participants who enroll in DPP, as well as rates of participation and engagement according to CDC standards (e.g., average number of sessions attended, proportion who completed > 9 and > 16 sessions, proportion with documented physical activity minutes, etc.). We will assess the representativeness of those who enrolled and participated in DPP as compared to the population overall, as well as the subset who were contacted for enrollment but chose not to enroll. We will also report exclusions, participation rates, drop-outs and representativeness within campuses and across UC.

We will examine the effectiveness of the DPP program (% weight change and DPP participation) within and between subjects. We will evaluate the consistency of outcomes across sites and key subgroups (e.g., race and ethnicity). We will also construct a logistic regression model to evaluate factors that predict whether subjects that receive the prediabetes letter will enroll in DPP. This is equivalent to the comparison of patient level factors between Group 1 and Group 2. First, we will use bivariate logistic regression models to evaluate subject level characteristics (e.g., age, gender, race, ethnicity, BMI, change in weight between the pre time point and baseline, income level) that predict the outcome. Next, we will construct a multivariable logistic regression model using a Least Absolute Shrinkage and Selection Operator (LASSO), [26] to identify the combination of factors that predict whether eligible subjects enroll in DPP (Group 1 vs. Group 2).

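### A p < 0.05 interaction screen over nine modifiers and two model forms decides whether the Group 1 models are stratified; with 50 people its false-trigger rate is about 37% to 60% and its power is low

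*Protocol article*

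**What the plan says.** All of the rule stands in the protocol article under Data collection & statistical analyses.

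- **Status.** "For both models, exploratory post-hoc analyses will also consider additional subject level covariates".
- **Candidates.** The covariates are "age, gender, race, ethnicity, number of co-morbidities, number of DPP sessions attended, education level and years employed at the institution", and DPP site is added. That makes nine.
- **What is tested.** "Interactions of the difference over time (rates or mean levels) by these subject characteristics or site will also be explored". Rates and mean levels correspond to the two mixed models described just before: the time-by-time-period interaction model and the time-period model.
- **Purpose.** The aim is "to evaluate whether there is a differential benefit of the program for certain groups of beneficiaries".
- **Rule.** The threshold is p < 0.05, and the consequence of crossing it is fixed: "interactions, the models will be stratified so as to allow for potential heterogeneity in the covariates as well".

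No adjustment across the interaction tests is mentioned. The sample size section gives Group 1 as 50 people, 10 at each of five sites. Under Aim 2 the protocol adds: "We will evaluate the consistency of outcomes across sites and key subgroups (e.g., race and ethnicity"; the Effectiveness row of Table 2 says much the same. Neither place repeats the exploratory label.

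**The concern.** The plan does more than look at subgroups. It sets a significance threshold in advance and attaches a modelling consequence to it, so a test result determines which models are fitted. With nine candidates, two model forms and a 5% level for each test, at least one interaction may well cross the threshold by chance. Because the sample is small, any interaction that does cross it will look large.

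The consequence also suits the data poorly. If site triggers, each stratified model rests on about 10 people, and the stated reason for stratifying is to let covariate effects differ between strata. At stake is a spurious or very imprecise subgroup or site finding in an evaluation meant to inform UC and other large employers.

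**Working it through.** **Inputs.** From the protocol: nine modifiers, two model forms, p < 0.05 per test, Group 1 N = 50 (10 per site), 80% power for a paired difference of 3.3%, more than 98% power for 5%, and 80% power for a between-group difference of 2.5% with 50 vs 500. Not given: the SD, and the correlation between the tests in the two models. Both are treated as ranges.

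**1. Reproduce the plan's own figures and recover the SD.**
- Paired, normal approximation: SD = 3.3 × √50 / (1.960 + 0.842) = 8.33. The noncentral t gives 8.16. About 8.2 is used below. Power for 5% is then 98.9%, which agrees with the stated figure.
- Between groups: SD = 2.5 / [(1.960 + 0.842) × √(1/50 + 1/500)] = 6.02. Power for 3% is then 92% (stated 90%), and the detectable difference for 550 vs 500 is 1.04% (stated 1.1%).
- The two statements therefore imply SDs of about 8.2 and 6.0. Both are carried forward.

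**2. Chance of at least one false trigger when no modifier has an effect.**
- One model, nine independent tests: 1 − 0.95^9 = 37.0%.
- Two models, 18 independent tests: 1 − 0.95^18 = 60.3%.
- Two models on the same people, with correlation ρ between the paired test statistics: 1 − P(|Z1| < 1.96 and |Z2| < 1.96; ρ)^9.

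| ρ | P(at least one false trigger) |
|---|---|
| 0 | 60.3% |
| 0.5 | 57.5% |
| 0.8 | 51.9% |
| 0.9 | 48.1% |
| 0.95 | 45.2% |
| 1 | 37.0% |

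The 50% line is crossed at ρ of about 0.86. Expected false hits: 9 × 0.05 = 0.45 per model and 18 × 0.05 = 0.90 over both.

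A null simulation (2,000 runs per setting, n = 50 and n = 40, assumed category mixes, one overall test per modifier) gave about 35% to 38% for one model. For two models it gave 58% to 61% at ρ = 0, about 57% at 0.5, 49% to 52% at 0.8 and 43% to 44% at 0.95.

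**3. What a significant interaction must look like.** A two-category modifier split 25/25 is an illustrative assumption. Critical difference = t(0.975, 48) × SD × √(1/25 + 1/25), with t = 2.011.
- SD 6.0: 2.011 × 6.0 × 0.2828 = 3.4 points.
- SD 8.2: 2.011 × 8.2 × 0.2828 = 4.7 points.

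Power for a true 2-point difference (noncentral t) is 21% with SD 6.0 and 13% with SD 8.2. If 50 is the enrolled number and 40 remain after 20% loss, the back-solved SDs shrink to 5.4 and 7.3, and a 20/20 split gives thresholds of 3.4 and 4.6 points, so the result barely moves.

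**4. What stratifying by site would give.** With 10 people per stratum, the 95% half-width of a mean change is t(0.975, 9) × SD / √10. That is 2.262 × 6.0 / 3.162 = 4.3 points, or 5.9 points with SD 8.2, before any covariate is added.

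**The case against.** The strongest reply is that the protocol already calls these analyses exploratory and post hoc. Family-wise error control is not usually required there, and no primary or secondary test depends on the screen. That stands, and it is why formal multiplicity control is not asked for. It does not rescue the trigger: exploratory status supports cautious reporting, not a significance test that selects the model. Nor is this a detail left to a fuller document, since the article states both the threshold and its consequence.

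Three stronger readings are tempting and are not supported.

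- **A false hit is more likely than not.** That holds for the two models together only if their tests correlate below about 0.86. They share the same people and weights, so a higher correlation is plausible, and one model alone gives 37%. The calculation also takes all nine modifiers as null, whereas sessions attended may have a real effect. Testing each category contrast separately would raise the rate, but the protocol does not say that this will be done.
- **A hit will replace the pooled result or be declared a differential benefit.** The protocol says only that the models will be stratified, and gives a modelling reason. It does not say that the pooled estimate is dropped.
- **The screen feeds the consistency statements in Aim 2 and Table 2.** Neither place cites the interaction tests or a p-value. The link is possible but not documented.

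**Conclusion.** The concern holds in a limited form. A fixed p < 0.05 rule over nine modifiers and two model forms leads to stratified models in a group of 50, with a false-trigger chance of about 37% for one model and roughly 45% to 60% over both. The rule also has little ability to find what it looks for: about 13% to 21% power for a 2-point difference, against an observed difference of 3.4 to 4.7 points needed for significance.

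The false-trigger figures assume no true heterogeneity, near-independence of the nine modifiers and a between-model correlation up to about 0.95. The size figures assume a 25/25 split and an SD between 6.0 and 8.2. The within-Group-1 primary analysis and the comparisons of Groups 1 vs 2 and Groups 1 + 2 vs 3 are not touched. This is a weak exploratory rule that is worth correcting, not a threat to the main conclusions.

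**What to change.** Under Data collection & statistical analyses, delete the sentence that makes stratification follow from p < 0.05. In its place:

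1. Estimate each subgroup and site difference from one pooled model, using a time-period × modifier term for mean levels, or a time × time-period × modifier term for rates.
2. Report all of these estimates with 95% confidence intervals, whatever their p-values.
3. Describe any subgroup or site difference as hypothesis-generating, and carry that wording into Aim 2 and the Effectiveness row of Table 2 wherever such estimates support a statement about consistency.

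Holm or false-discovery-rate control is optional; statisticians differ on it for exploratory subgroups.

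The cost is wording only. The one loss is that covariate effects may no longer differ freely between strata, which strata of about 10 people could not estimate reliably in any case.

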### Aim 1: effectiveness of UC DPP

To assess the effectiveness of the UC DPP Initiative, we will examine mean percent weight change from baseline at 12 month follow-up and 24 month follow-up within and between three groups of overweight/obese UC beneficiaries. Group 1 includes overweight/obese beneficiaries with documented prediabetes who receive UC DPP Initiative prediabetes awareness letters and enroll in DPP (i.e., receive “full treatment”). Group 2 includes overweight/obese beneficiaries with documented prediabetes who receive UC DPP Initiative prediabetes awareness letters, but do not enroll in DPP. Group 3 includes overweight/obese UC beneficiaries without documented prediabetes who are not included in the UC DPP Initiative (do not receive prediabetes awareness letters and do not enroll in DPP). Group 3 serves as a control group to account for secular trends and/or concurrent programs that may affect weight change outcomes among UC beneficiaries (such as weight management services any overweight/obese UC beneficiaries may receive as part of routine care). The primary outcome will be % weight change at 12-month follow-up within those who received a “full intervention dose” (i.e., Group 1) and secondary outcomes will compare mean % weight change between UC beneficiaries (Groups 1 vs. 2 and Group 1 + 2 vs. Group 3).

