
We will also compare outcomes between UC beneficiaries in Groups 1 vs. 2, a between-subject comparison, to estimate DPP effectiveness while holding the effect of the prediabetes awareness campaign constant across groups (both Group 1 and 2 receive prediabetes outreach letters). The mixed effects models mentioned above will be modified to examine between group differences in within-person change by incorporating an interaction term with Group membership. Similarly, we will compare outcomes in Groups 1 + 2 vs. Group 3, a between-subject comparison akin to an intent-to-treat (ITT) analytic approach since outcomes are being assessed among all UC beneficiaries with documented prediabetes eligible to receive the UC DPP Initiative in comparison to similarly overweight/obese individuals not exposed to the program. We will use propensity score matching to identify comparable overweight/obese beneficiaries with (Groups 1 + 2) and without (Group 3) documented prediabetes. The propensity score model will include baseline age, gender, race/ethnicity, BMI, and medical co-morbidities. Matching will be accomplished through use of the nearest-neighbor algorithm. Between group balance in the propensity scores and covariates will additionally be examined. While Groups 1 and 2 have an easily defined baseline for differentiating between pre- and post- diabetes awareness (i.e., enrollment or awareness letter date), Group 3 will have their baseline selected as corresponding to 12–18 months (or 24–30 months) prior to their most recent EHR entry.

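### The secondary Group 1 vs Group 2 contrast is offered as an estimate of DPP effectiveness, but enrolment is self-selected and no confounder adjustment is pre-specified for it

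*Protocol article*

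**What the plan says.** All places are in the Methods of the protocol article.

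- **Groups (Aim 1).** Group 1 are beneficiaries with documented prediabetes "who receive UC DPP Initiative prediabetes awareness letters and enroll in DPP". Group 2 are those "who receive UC DPP Initiative prediabetes awareness letters, but do not enroll in DPP".
- **Status (Aim 1).** The primary outcome is within Group 1; "secondary outcomes will compare mean % weight change between UC beneficiaries (Groups 1 vs. 2 and Group 1 + 2 vs. Group 3").
- **Purpose (Data collection & statistical analyses).** Group 1 vs 2 is made "to estimate DPP effectiveness while holding the effect of the prediabetes awareness campaign constant across groups".
- **Model (same section).** "The mixed effects models mentioned above will be modified to examine between group differences in within-person change by incorporating an interaction term with Group membership". Those models compare each person's pre-enrolment and post-enrolment percent weight change, with random effects for person.
- **Adjustment for the other contrast (same paragraph).** Nearest-neighbour propensity matching and a balance check are described for Groups 1 + 2 vs Group 3: "The propensity score model will include baseline age, gender, race/ethnicity, BMI, and medical co-morbidities".
- **Other covariates (same section).** "For both models, exploratory post-hoc analyses will also consider additional subject level covariates". The list includes the number of DPP sessions attended. Separately, covariates that differ by attrition status at p < 0.05 are added to support the missing-at-random assumption.
- **Enrolment model (Aim 2).** Logistic and LASSO models predict enrolment among people who received the letter. Candidates include BMI, income and weight change before baseline. The article remarks: "This is equivalent to the comparison of patient level factors between Group 1 and Group 2".

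**The concern.** This is the only between-person contrast meant to separate DPP from the awareness letter, and the Background faults earlier university studies for lacking comparator groups. A reader will therefore rely on it for a causal statement about DPP. Group membership is the person's own decision, and Aim 2 treats that decision as something BMI, income and recent weight change may predict. If any of these, or motivation, also affects how weight changes after baseline, the Group interaction carries that effect together with the effect of DPP. The article does not plan to separate the two in the main analysis of this contrast.

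**Working it through.** **Step 1. Where covariates enter, and whether they serve Group 1 vs 2.**

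| Use of covariates | Applies to Group 1 vs 2? | Controls confounding? |
|---|---|---|
| Propensity matching and balance check | No; described for 1 + 2 vs 3 | Not for this contrast |
| Exploratory post-hoc list | Possibly, through the modified model | Not the planned analysis; omits income and prior weight change; sessions attended follows from enrolment |
| Attrition-triggered covariates | Possibly | Chosen for dropout, so a strong confounder unrelated to dropout would not enter |
| Aim 2 enrolment model | It models exactly this choice | Never linked to the effect estimate |

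**Step 2. What the within-person structure removes.** With Group interacted, the model is in effect a difference-in-differences. Stable differences in weight are removed, and the rate model also removes a stable linear difference in trend. Selection that changes around enrolment remains. If people enrol after a recent gain that would have levelled off anyway, the levelling-off appears as a pre/post improvement in Group 1.

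**Step 3. Reproduce the plan's power (Sample size and power calculations).** Inputs: 50 vs 500, two-sided alpha 0.05, t-test, 90% power for 3%, 80% power for 2.5%. No SD is given, so it is back-solved with the noncentral t.

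- 80% at 2.5% implies SD 6.01, which gives 92.0% power at 3% (stated 90%).
- 90% at 3% implies SD 6.23, which gives a detectable difference of 2.59% (stated 2.5%).
- If 40 vs 400 remain after the 20% loss, the implied SDs are 5.37 and 5.57. The implied SE hardly changes: 6.23 × √(1/50 + 1/500) = 0.924 and 5.57 × √(1/40 + 1/400) = 0.924.

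The stated power figures agree with each other within rounding. They concern precision and say nothing about bias.

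**Step 4. Size of the bias (illustration).** Let b be the difference in weight change that selection alone would produce. Every value of b is an assumption. The last column is the chance of a significant result if DPP had no effect, with 50 vs 500 and SD 6.0 to 6.25.

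| b (points) | b / 3 | Chance of significance (nominal 5%) |
|---|---|---|
| 0.5 | 17% | 8-9% |
| 1.0 | 33% | 19-20% |
| 1.5 | 50% | 37-39% |
| 2.0 | 67% | 58-61% |

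Check at b = 1.0 with SD 6.1 and the normal approximation: SE = 6.1 × √(1/50 + 1/500) = 0.905; 1.0/0.905 = 1.105; Φ(1.105 − 1.96) + Φ(−1.105 − 1.96) ≈ 0.20.

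**Step 5. Precision cost of adjusting.** Power ≈ Φ(3/SE − 1.96), SD 6.1, SE = 6.1 × √(1/n1 + 1/n2). The effective sizes under weighting are assumptions.

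| Effective n1, n2 | SE | Power for 3% |
|---|---|---|
| 50, 500 (unweighted) | 0.905 | 91% |
| 50, 250 | 0.945 | 89% |
| 50, 100 | 1.057 | 81% |
| 35, 250 | 1.101 | 78% |

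Matching without replacement with 50 in Group 1 (noncentral t, SD 6.0 to 6.25) gives about 66-70% at 1:1, 79-82% at 1:2 and 86-88% at 1:4.

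**The case against.** The strongest reply is that each person serves as their own control, so much of what distinguishes enrollees is already removed. That stands, and it narrows the point to time-varying selection. A reader might infer that the contrast estimates DPP plus everything that makes enrollees different; the pre/post model does not support so broad a statement.

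A reader might also infer that no adjustment of any kind is foreseen. The exploratory list and the attrition covariates could both carry over to the modified model. What the text supports is that no confounder adjustment is pre-specified for this contrast.

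Matching in the other contrast has a further purpose: it selects a control pool from people outside the initiative. Group 2 shares the diagnosis and the letter and needs no such selection. That is fair, but shared eligibility does not make the decision to enrol ignorable. The planned 10 and 100 per site would limit campus imbalance if they are met.

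An article condenses the full plan, which may add covariates. This remains possible. Still, one paragraph sets out an adjustment method, covariates and a balance check for one contrast and only an interaction for the more self-selected one. That is a stated choice of method, so the point is not just a missing detail.

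Finally, no passage establishes the direction or size of the bias. That is correct, and the figures for it are illustrations only.

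**Conclusion.** The point holds for the secondary Group 1 vs 2 contrast. Followed as written, the estimate is open to confounding by time-varying selection, yet it is described as DPP effectiveness. The size is unknown: assumed selection differences of 0.5 to 2.0 points would make up 17% to 67% of the planned 3%. With no DPP effect they would give a significant result in roughly 8% to 61% of studies. These figures rest on an SD back-solved from the stated power and on the t-test simplification that the article itself uses.

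Three stronger readings are not supported:

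- That the primary result is undermined. The primary analysis is within Group 1 and does not depend on this comparison.
- That the propensity model for Groups 1 + 2 vs 3 is wrong because it leaves out campus and prior weight change. Nothing in the article shows that omission to be an error.
- That adjustment costs almost nothing. The 89% figure is a favourable case; other plausible effective sizes give about 78% to 81%.

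**What to change.** 1. Pre-specify baseline adjustment for Group 1 vs 2 with a short set of pre-enrolment variables the article already plans to use: age, gender, race/ethnicity, baseline BMI, co-morbidities, income and site.
2. Enter them as covariates with their time-period interactions, or use them in propensity weights. A main effect alone shifts the level and does not adjust the pre/post change.
3. Report covariate balance between the two groups, and leave out sessions attended.
4. Compare pre-period weight trends between the groups. Keep weighting on prior weight change as a sensitivity analysis: pre-period weights are already part of the modelled response, and conditioning on them can itself bring in regression to the mean.
5. Report the unadjusted contrast alongside, and describe the result as an association subject to residual self-selection, since measured covariates cannot capture all of motivation.

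The cost is analysis-plan wording, programming and some precision. Covariate adjustment keeps all 550 people. Weighting may lower power for 3% from about 91% to roughly 78-89% under the effective sizes assumed above. With 50 enrollees (40 after the 20% loss) and multi-level factors such as site and race/ethnicity, a long propensity model would be unstable, so the set should stay small. If 1:1 matching were chosen instead, the stated 90% power would no longer apply.

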Mixed methods study of engagement in behaviors to prevent type 2 diabetes among employees with pre-diabetes, 2016 [16]	﻿University of Michigan	Pre and post mixed methods study	﻿Facilitators of and barriers to engagement in recommended behaviors	82 (23 M, 59 F)	3 months	N/A	﻿Key facilitators of engagement included assistance and encouragement from social networks as well as use of external supports such as tracking devices. Barriers to engagement included competing demands and insufficient resources ﻿for healthy behaviors.

Beginning in 2018, the UC System  implemented the UC DPP Initiative, which is a multi-component program to target diabetes and obesity prevention among at risk affiliates. This initiative was informed by a pilot DPP implemented at the University of California Los Angeles (UCLA) in 2016. UCLA DPP was one of the first university-based programs in the US to achieve full CDC recognition. CDC recognition is granted to programs that meet all recommended milestones for DPP delivery, including 5% mean weight loss among participants. Based on the success of the UCLA campus-wide DPP, campus leaders and researchers partnered with the UC Office of the President (UCOP) and UC Health to launch a UC-wide DPP Initiative in 2018. By 2019, all 10 UC campuses had implemented UC DPP, which now operates as part of routine campus activities (more details below). To our knowledge, this is one of the largest university-based efforts to adress diabetes and obesity prevention with a focus on system-wide DPP-based ILI delivery.

Our goal is to conduct a rigorous, mixed-methods evaluation of the UC DPP Initiative, focusing on the five UC campuses with large medical centers where robust EHR data for UC beneficiaries is also available; namely UC Los Angeles, Irvine, San Diego, San Francisco, and Davis. Our goals are to identify why the UC DPP Initiative succeeds (or not), and to document lessons learned across the UC system and between campuses to inform future efforts across UC and other large university systems.

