### Sample size and power calculations

For our primary outcome of % weight change at 12-month follow-up within subjects, we will use 5% weight change to estimate power based on the 2002 DPP randomized controlled trial [4] as well as National DPP recognition standards [22]. With a proposed sample size of *N* = 50 using a two-sided alpha level of 0.05, we would demonstrate 80% power to detect a paired difference of at least 3.3% and have > 98% power to detect our target weight change of 5%. For our outcome of weight change at 12-month follow-up between subjects, we conservatively assume that the average % weight loss for those in Group 2 (prediabetes notified) and Group 3 (usual care) will be 2 and 0% respectively. These values will yield about a 3% difference in weight loss between our comparison groups. Using an independent samples t-test as a simplification of the mixed effects analysis plan with a two-sided alpha of 0.05, we will have 90% power to detect our assumed between group difference of 3% with the proposed sample sizes of 50 (Group 1; 10 per site) and 500 (Group 2; 100 per site). Using the same assumptions, the proposed sample sizes of *N* = 550 Group A + B and *N* = 500 Group 3 would yield 99% power to detect the assumed 3% difference in the percentage weight change between the groups. We would additionally have 80% power to minimally detect a between group difference of 2.5 and 1.1% with these sample sizes. All sample sizes account for an anticipated 20% loss to follow-up [7]. We will not be powered to detect differences in rates of incident type 2 diabetes, but we will examine trends over time using validated EHR and claims data algorithms [23, 24]. Metformin is not specifically highlighted in the UC DPP Initiative, but since some beneficiaries with prediabetes may also seek out this option, [4, 25] we will also examine rates of metformin uptake using prescription data available in the EHR.

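### Campus is absent from the stated matching variables and Group 3 has no number per site, which leaves the secondary Groups 1 + 2 versus Group 3 comparison open to a probably modest campus bias

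*Protocol article*

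**What the plan says.** All references are to the protocol article.

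- **Purpose of Group 3** (Aim 1: effectiveness of UC DPP): "Group 3 serves as a control group to account for secular trends and/or concurrent programs that may affect weight change outcomes among UC beneficiaries". The example given is "such as weight management services any overweight/obese UC beneficiaries may receive as part of routine care".
- **Setting** (end of the Background): the evaluation is "focusing on the five UC campuses with large medical centers where robust EHR data for UC beneficiaries is also available".
- **Selection of Group 3** (Data collection & statistical analyses): "The propensity score model will include baseline age, gender, race/ethnicity, BMI, and medical co-morbidities". The next sentences add "Matching will be accomplished through use of the nearest-neighbor algorithm" and "Between group balance in the propensity scores and covariates will additionally be examined". Within-campus matching is not mentioned.
- **Numbers** (Sample size and power calculations): the first two groups are planned at "50 (Group 1; 10 per site) and 500 (Group 2; 100 per site". Group 3 is 500 in total with no split by site, to be compared with 550 from Groups 1 and 2 together (labelled A + B there).
- **Site in the models** (Data collection & statistical analyses): DPP site is one of several covariates and interactions for exploratory post-hoc analysis. Table 2 and the Aim 2 section also plan to look at the consistency of outcomes across sites.
- **Rank of the comparison** (Aim 1): Groups 1 + 2 versus Group 3 is secondary. The primary outcome is weight change within Group 1.

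**The concern.** A control group meant to absorb the effect of concurrent programmes should face the same programmes as the people it is compared with. Five campuses with separate medical centers may well offer different weight-management and wellness services, or change them at different times. The listed matching variables would not prevent controls from being drawn mainly from one or two campuses. The balance check would not clearly reveal this either, because campus is not among the listed covariates.

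This is the only comparison with people outside the initiative, and the protocol likens it to an intention-to-treat analysis. If the campus mix differs between the two sides, and background weight trends shift differently by campus over the study period, part of that shift would be read as an effect of the initiative.

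**Working it through.** **1. Campus shares that the plan implies.** Groups 1 + 2 have 10 + 100 = 110 people per site. Over five sites that is 550, so each campus holds 110/550 = 20%. For Group 3 no share can be derived. An equal split would be 500/5 = 100 per site, also 20%, but nothing stated secures it.

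**2. The plan's own figures, to obtain a scale.** The SD is not stated, so it is back-solved from the detectable differences at 80% power (two-sided alpha 0.05, two-sample t-test).

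- 50 versus 500, difference 2.5: SD about 6.0.
- 550 versus 500, difference 1.1: SD about 6.3.
- With these SDs, power for a 3-point difference is 89% to 92% for 50 versus 500 (stated 90%) and above 99.9% for 550 versus 500 (stated 99%).

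The figures agree within rounding. Taking SD = 6.1, the standard error of the Groups 1 + 2 versus Group 3 contrast is 6.1 × √(1/550 + 1/500) = 0.377 points.

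**3. When does a bias arise?** Let campus *i* have a background shift *m_i*, and let Group 3 have campus shares *p_i*. The size of the error in the mean difference is |Σ(*p_i* − 0.2)·*m_i*|. It is zero if all *p_i* = 0.2, even when every matched pair crosses campuses. It is also zero if the *m_i* are equal. Both unequal shares and unequal shifts are needed.

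**4. Illustration with a random campus shift (assumed inputs).** Assume Group 3 shares of 40/20/15/15/10% and a between-campus SD τ of 0.5 to 1.0 points.

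- Σ(*p_i* − 0.2)² = 0.04 + 0 + 0.0025 + 0.0025 + 0.01 = 0.055, and √0.055 = 0.2345.
- Error SD = 0.2345 × τ = 0.117 points for τ = 0.5 and 0.235 points for τ = 1.0.
- Type I error = 2·P(Z > 1.96 × 0.377/√(0.377² + error SD²)) = 6.1% and 9.6%, against a nominal 5%.

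**5. Illustration with a fixed campus pattern (assumed inputs).** Let two campuses lie at the top of a range *R*, one in the middle and two at the bottom, with the larger Group 3 shares at the top.

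| Group 3 shares (%) | Bias formula | R = 0.5 | R = 1 | R = 2 |
|---|---|---|---|---|
| 20/20/20/20/20 | 0 | 0 | 0 | 0 |
| 35/25/20/10/10 | 0.2 × R | 0.1 | 0.2 | 0.4 |
| 40/30/20/5/5 | 0.3 × R | 0.15 | 0.3 | 0.6 |

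**6. What steps 4 and 5 leave out.** They treat the comparison as a simple two-group contrast of 12-month change. The planned model compares groups on within-person change between the pre and post periods. A campus difference in trend that is the same in both periods drops out, and only a campus-specific change between the periods remains. If campus shifts have SD τ in each period and correlation ρ between periods, the SD of what remains is τ√(2(1 − ρ)). This is below τ whenever ρ exceeds 0.5. The results are therefore upper illustrations as long as campus differences are mostly stable.

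**The case against.** The case on the other side is substantial, and much of it stands.

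- **No text says that concurrent programmes differ by campus.** A reader might infer it as a documented fact. The one example is routine-care services open to any overweight or obese beneficiary. Campus differences are a plausible inference from separate medical centers and campus-run wellness services, and the plan itself looks for site differences, but they remain an inference.
- **Differences in how weight is recorded are no argument here.** The data collection section says that EHR weights are collected similarly across the health centers.
- **Not every campus difference enters the estimate.** The pre/post structure would largely remove stable differences in trend. Cross-campus pairs alone do no harm if the overall shares are alike.
- **Site is not wholly ignored.** The between-group models are adaptations of those in which site may be explored, and consistency across sites is to be reviewed. That use in the models is exploratory, however, and the variable is DPP site, which is not naturally defined for people who never enroll.
- **Matching detail often belongs in a fuller analysis plan.** Within-campus matching is not excluded, and the missing per-site number for Group 3 may be condensation. But the article does state the covariate list and the algorithm, and as stated they do not secure what Group 3 is for.
- **The comparison is secondary, and the illustrated error is small** beside the assumed 3-point difference.

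These points limit the size and rank of the concern. They do not supply a stated safeguard.

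**Conclusion.** The point holds in a limited form. The stated matching variables omit campus, no within-campus matching is described, and Group 3 has no number per site, whereas Groups 1 and 2 are planned equally over five sites. The secondary Groups 1 + 2 versus Group 3 comparison is therefore exposed to bias if two conditions hold together: Group 3's campus mix differs from 20% each, and background weight trends change differently by campus between the pre and post periods.

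The documents do not give the size. Under assumed shares and an assumed between-campus SD of 0.5 to 1.0 points, ignoring the pre/post cancellation, the error SD is about 0.1 to 0.2 points, against a stated detectable difference of 1.1. The effect is probably modest. A reader might conclude that Group 3 cannot serve as a control at all. That does not follow: its adjustment for system-wide secular trends is untouched, and the campus bias is conditional. The primary within-Group 1 analysis uses no matching and is unaffected.

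**What to change.** 1. Run the nearest-neighbour propensity match separately within each of the five campuses. If that leaves too few candidates at a campus, add campus to the propensity model instead and include it in the balance table.
2. State Group 3 numbers per site so that they mirror Groups 1 + 2. With the planned totals that is 100 per campus.
3. Include campus as a fixed effect in the Groups 1 + 2 versus Group 3 model, with its interaction with time period. A campus main effect alone takes up only stable differences, which the pre/post contrast already largely removes.

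The cost is a few lines in the analysis plan and a smaller pool of candidate controls per campus, which may make some matches less close on the other covariates. The protocol does not state that campus is recorded for every beneficiary. It does plan Groups 1 and 2 by site and draws on the EHR data of the five campuses, so the variable should be available.
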